## **Purpose of the Statistical Analysis Plan**

In the following, we describe the statistical analysis plan (SAP) for a cross-sectional study on pulmonary disease among patients with systemic lupus erythematosus in the Southern Denmark Region. The purpose of this SAP is to outline our planned analyses for the study "Prevalence and Types of Concomitant Pulmonary Disease in Systemic Lupus Erythematosus: A Population-Based Cross-Sectional Study." Given the observational nature of the study and the large number of variables, we consider it essential to ensure transparency in our analytical approach. The study has been registered at ClinicalTrials.gov (NCT06087523), but no protocol has been published. Data on pulmonary disease (PD) diagnoses and high-resolution computed tomography (HRCT) evaluations are stored in a Research Electronic Data Capture (REDCap) database and remain blinded to the statistician, principal investigator, and statistical advisor until this statistical analysis plan is finalized and signed.

## INTRODUCTION

Systemic Lupus Erythematosus (SLE) is a systemic autoimmune disease that may affect any organ. SLE is mostly associated with haematological abnormalities, rashes, arthritis/arthralgia, nephritis, and constitutional symptoms (1). Pulmonary diseases are common among SLE patients and affect up to 70% of the patients (2, 3), but the prevalence of PD among SLE patients are not investigated in a clinical study with a population-based design, to our knowledge. Prior studies have mostly investigated specific subgroups of PD and not PD in general. The PD commonly associated to SLE are airway disease, pleural disease, interstitial lung diseases (ILD), vasculitis, pulmonary haemorrhage, pulmonary hypertension, and the syndrome "Shrinking Lung Syndrome" (2-4).

Pulmonary Disease among SLE patients are important, as they are associated to an increased mortality (5) and decreased health-related quality of life (6). Unfortunately, there are a substantial difference between how patients report pulmonary symptoms and how physicians rate PD (7). It can be difficult to diagnose PD among SLE patients, for instance ILD is reported with a prevalence of 11-37% in clinical studies at tertiary centres (8-11) but only around 6% in register studies (12). To diagnose PD among SLE patients, healthcare providers need to have suspicion. We believe that a detail knowledge of how common different PD are among SLE patients will help guide physicians to be aware of which PD they should suspect and maybe subsequently investigate. Importantly, a study have shown, that immunosuppression can improve pulmonary function among SLE patients (13).

It is not always clear if pleura, pulmonary vasculature, and diaphragm are covered by the term "pulmonary disease". In the following we will refer to diseases of the pleura, airways, pulmonary vasculature, diaphragm, and lung parenchyma as pulmonary diseases (PD).

## Objectives

The primary objective is to determine the prevalence of concomitant PD among SLE patients in a prospectively designed cross-sectional study.

Secondary objectives, based on the same primary sample of SLE patients to evaluate the:

- Baseline characteristics and outcome measures, overall and stratified by the presence or absence of PD
- Pulmonary function test (PFT) results, overall and stratified by the presence or absence of PD
- Prevalence of specific PD subtypes
- Associations between baseline characteristics and outcome measures and the presence of PD and selected pre-defined subtypes of PD

## METHODS

The present study is part of a larger research initiative. Findings on the associations between PD and PD subtypes and pulmonary function test (PFT) measures, thoracic ultrasound, diaphragmatic ultrasound, and additional biomarkers will be reported in separate publications. A separate study will examine PD diagnoses and selected outcomes, including thoracic and diaphragmatic ultrasound, in newly diagnosed systemic lupus erythematosus (SLE) patients. Patients were identified through a systematic search of hospital records across all institutions in the Southern Denmark Region. The search includes visits between July 1, 2021, and June 30, 2023, coded as related to SLE or SLE-associated diseases. Participants were enrolled between August 1, 2023, and October 31, 2024. Statistical analyses will commence upon finalization and approval of this SAP.

At a single visit day all tests were performed. All participants start with an outpatient visit, where the primary investigator review the participants' medical history, note the patients' disease activity and damage. Hereafter the participants undergo pulmonary function testing, HRCT scan, and blood and urine samples. Questionnaires are filled out before the visit. The HRCT scans are described after the visits, and finally the participants are diagnosed, at a multidisciplinary discussion (MDD). The study will be reported in accordance with the STROBE guideline (Strengthening of Reporting Observational Studies in Epidemiology). It is not always possible to measure a precise saturation in a six-minute walk test, why we have scored them as good, medium, poor, too bad to use. Good is tests without any outages. Medium is tests with outages, that which we do not suspect affect the measurement. Poor is tests where we suspect, that the outages affect the results. We will only use tests that score good or medium, and the rests will be regarded as missing values.

## **Statistical analyses**

### **Analysis populations**

The primary analyses will be based on the Intention to Survey (ITS) population (14). This principle assesses the effect of all participants investigated for PD stratified by the presence of PD and subtypes of PD. Accordingly, participants allocated to a PD group will be assessed and analysed as members of that group, irrespective of the availability of the various collected characteristics and outcome variables.

### **Baseline patient characteristics: Descriptive statistics**

Mock-up Table 1. Descriptive statistics at baseline in a study like the present summarize the key characteristics of the study population to provide an overview before any interventions or outcomes are analysed. These statistics typically include demographic characteristics (e.g., age, sex, ethnicity), clinical characteristics (e.g., comorbidities, medication use), lifestyle factors (e.g., smoking status), and laboratory data (e.g., blood samples). Continuous variables will be summarized by means and standard deviations (SD) or medians and interquartile ranges (IQR), while categorical variables will be presented as frequencies and percentages. When the cross-sectional sample is divided into subgroups (e.g., PD vs. No PD), baseline characteristics will be compared using standardized differences (Std. Difference) to assess balance across groups; they are independent of sample size, allowing for a consistent measure of covariate imbalance without being influenced by statistical significance. These descriptive statistics will be presented in tables for clarity, and their purpose is to characterize the cohort, assess comparability between groups, and provide context for interpreting the study's results. Interpretation of standardized differences include  $<0.1$  indicates a negligible difference; values between 0.1 and 0.2 might suggest a small difference, and  $>0.2$  may indicate an imbalance.

### **Comparing the SLE population: Analysis methods comparing PD exposed with PD-unexposed**

Mock-up Table 2. We will compare baseline characteristics across SLE strata, including Systemic Lupus Erythematosus activity and damage scores, patient-reported outcome measures, and pulmonary function tests, for all patients and by the presence or absence of thoracic disease. All 95% confidence intervals (95%CI) will be two sided. The analyses of the secondary outcomes will be performed in sequence. The 95%CI will not be adjusted for multiplicity and should not be used in place of hypothesis testing.

### **Prevalence of groups and subgroups of pulmonary diseases: Descriptive statistics**

Mock-up Table 3. We will describe the prevalence of specific groups (e.g. airway disease, ILD) and subgroups (e.g. asthma, bronchiectasis, atelectasis) of PD among the study participants. We plan to present the prevalence with absolute numbers and proportion as percentages.

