| Desaturation, (Saturation delta)         |     |            |           |                                 |
| Desaturation below 93% #, no. %          |     |            |           |                                 |

Value will be means and SDs unless otherwise indicated. \* - % of expected; \*\* - low is defined as below 80% of expected; # - If COPD or emphysema 88%. SLE – Systemic Lupus Erythematosus; PROMs – Patient Reported Outcome Measures; PFT – Pulmonary Function Tests; PD – Pulmonary Disease according to multidisciplinary discussion; APL– Antiphospholipid Antibodies; dsDNA – anti-double stranded DNA antibodies; SLEDAI 2K – Systemic Lupus Erythematosus Disease Activity Index 2000 (16); PGA – Physician Global Assessment (17); LLDAS – Lupus Low Disease Activity State (18); DORIS – Definition of

Remission in SLE (19); SLICC DI – Systemic Lupus International Collaborating Clinics /American College of Rheumatology Damage Index for Systemic Lupus Erythematosus (20); LIT – questionnaire inspired by “Lupus Impact Tracker” (21); SLAQ – Systemic Lupus Activity Questionnaire (22); MRC – Medical Research Council Dyspnoea Scale; FEV1 – Forced Expiratory Volume in One Second; FVC – Forced Vital Capacity; TLC – Total Lung Capacity; DLCO - Diffusing capacity of the Lung for Carbon Monoxide; KCO – Carbon Monoxide Transfer Coefficient.

We plan to present the prevalence of subgroups of PD in a table, see table 3.

**Table 3.** Diagnoses of pulmonary diseases among Systemic Lupus Erythematosus patients.

| Groups of PD | Subgroups of PD                 | Prevalence, no. (%) |
|--------------|---------------------------------|---------------------|
| Airway       |                                 |                     |
|              | Asthma                          |                     |
|              | Bronchiectasis                  |                     |
|              | Obliterative Bronchiolitis      |                     |
|              | Infectious Bronchiolitis        |                     |
|              | COPD                            |                     |
|              | Emphysema                       |                     |
|              | Other                           |                     |
| Pleural      |                                 |                     |
|              | Pleuritis                       |                     |
|              | Pleural disease of diaphragm    |                     |

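### Overall PD prevalence is the primary objective, yet the SAP gives it no analysis section, no table row and no confidence interval

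*SAP*

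**What the plan says.** The Objectives section states: "The primary objective is to determine the prevalence of concomitant PD among SLE patients in a prospectively designed cross-sectional study". The prevalence of specific PD subtypes is listed separately, among the secondary objectives.

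One section of the statistical methods deals with prevalence. Its scope is: "We will describe the prevalence of specific groups (e.g. airway disease, ILD) and subgroups (e.g. asthma, bronchiectasis, atelectasis) of PD among the study participants". Its method is: "We plan to present the prevalence with absolute numbers and proportion as percentages".

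The matching shell, Table 3, has rows for six groups (airway, pleural, ILD, shrinking lung syndrome (SLS), vascular, other) and their subgroups. Its single results column has a heading that begins "Prevalence, no" and continues with a percentage. The footnote makes the total study population the denominator. There is no row for any PD and no column for an interval.

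Intervals are planned elsewhere: for the PD-present versus PD-absent contrasts in Table 2, for the differences in Appendix 1a to 1d, and for every odds ratio in Table 4 and Appendix 3.

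**The concern.** A prevalence study delivers one main number, and that number needs a defined place in the results and a statement of its precision. Here the subtype percentages have a table, and the exploratory odds ratios have a table and intervals. The overall prevalence has neither. It would appear only implicitly, as the size of the PD-present column in Tables 1 and 2, and those shells show no N in the column headings.

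Adding up the Table 3 groups is not a safe substitute. Nothing in the SAP says that the groups exclude one another, and Table 4 treats each as its own yes/no outcome.

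At stake is how firmly the result can be set beside earlier work. The Introduction cites up to 70% for PD overall and, for ILD, 11-37% in tertiary-centre studies against about 6% in registers. A bare percentage does not show whether a new figure agrees or disagrees with these within sampling error.

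**Working it through.** **Step 1. Trace the primary quantity through the SAP.**

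| Place in SAP | Quantity | Interval planned? |
|---|---|---|
| Objectives | Overall PD prevalence (primary) | No method given |
| Prevalence section and Table 3 | Groups and subgroups (secondary) | No: count and % |
| Table 1 | PD present vs absent | No: standardised difference |
| Table 2 | PD present vs absent | 95% CI |
| Appendix 1a-1d | Subtype present vs absent | 95% CI |
| Appendix 2 | HRCT findings | No: count and % |
| Table 4, Appendix 3 | Odds ratios, including for overall PD | 95% CI |

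The section comparing PD-exposed with PD-unexposed patients says that all 95% intervals will be two-sided. That sets sidedness for intervals planned elsewhere. It does not commit to one for prevalence.

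**Step 2. Is there a figure to reproduce?** No. The SAP states no sample size, precision target or prevalence result. Every N below is an assumption.

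**Step 3. Size of the missing interval.** The Wilson 95% interval for an observed proportion p in n patients, with z = 1.96, is

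[p + z²/(2n) ± z·√(p(1−p)/n + z²/(4n²))] / (1 + z²/n).

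For p = 0.50 and n = 100, z²/n = 0.0384 and the centre is 0.50. The half-width is 1.96 × √(0.0025 + 0.000096) / 1.0384 = 0.096, giving 40.4% to 59.6%.

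| Assumed n | Interval at 50% | Half-width (points) |
|---|---|---|
| 100 | 40.4% to 59.6% | 9.6 |
| 150 | 42.1% to 57.9% | 7.9 |
| 200 | 43.1% to 56.9% | 6.9 |
| 300 | 44.4% to 55.6% | 5.6 |

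**Step 4. Subtypes.**
- ILD at 6% (the register figure in the Introduction): 6 of 100 gives 2.8% to 12.5%; 12 of 200 gives 3.5% to 10.2%. The first interval contains 11%, the low end of the tertiary-centre range, and the second does not. The same bare 6% would therefore support different readings.
- One case, as the deviations section reports for SLS: the exact (Clopper-Pearson) interval is 0.03% to 5.4% for n = 100, 0.01% to 2.75% for n = 200, and 0.01% to 1.8% for n = 300.

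**Step 5. Non-participation, for illustration only.** With participation r, prevalence p in participants and q in eligible non-participants, the source prevalence is r·p + (1−r)·q. Take p = 50% and q between 30% and 70%.
- r = 60%: 0.6×50 + 0.4×30 = 42%, to 0.6×50 + 0.4×70 = 58%.
- r = 80%: 0.8×50 + 0.2×30 = 46%, to 0.8×50 + 0.2×70 = 54%.

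The SAP supplies neither r nor q, so this shows sensitivity and not a demonstrated bias.

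**The case against.** Several points on the other side stand.

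- The sentence giving counts and percentages governs groups and subgroups. It does not fix the primary estimate as a bare percentage. The accurate statement is that the SAP fixes nothing for overall PD.
- A reader might infer that the primary result alone is denied an interval while every secondary comparison has one. That is not so: Table 1 uses standardised differences without intervals, and Appendix 2 gives counts and percentages.
- A reader might set the headline against the 6% and 11-37% figures. Those are for ILD. Only the 70% figure concerns PD overall.
- Anyone given the count and the denominator can compute an interval. That is true, but the overall count has no assigned place in the tables, and a primary result should not rely on readers finishing the analysis.

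The stronger reading is that the estimate is biased by non-participation and must be weighted. It is tempting because the title calls the study population-based ("Prevalence and Types of Concomitant Pulmonary Disease in Systemic Lupus Erythematosus: A Population-Based Cross-Sectional Study"), because "Patients were identified through a systematic search of hospital records across all institutions in the Southern Denmark Region", and because the Introduction says of pulmonary diseases that "they are associated to an increased mortality". The search covered visits up to June 2023, and enrolment ran from August 2023 to October 2024. The document does not support that reading:

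- It gives no participation figures.
- The Figure 1 flowchart, captioned as covering possible participants, is not visible in the text at hand.
- The search list includes SLE-associated codes, so it is not a list of confirmed SLE patients.
- Patients who died before the survey are not part of the living population whose prevalence is measured at that time.
- Weighting on age, sex and hospital would not directly address selection by illness or symptoms.

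**Conclusion.** The point holds as a gap in specification and reporting. The primary objective has no analysis section, no table row and no interval, while the Table 2 and Appendix 1 contrasts and all odds ratios have intervals. Closing the gap changes neither the data nor the point estimate. It adds the precision that the headline now lacks: about 6 to 10 percentage points either side at 50% prevalence, if N lies between 100 and 300. Those sizes rest on an assumed N and an assumed prevalence. The absence of the row and the interval rests on the text alone.

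No required correction for non-participation follows from this document. Whether the population-based label needs qualifying depends on participation figures that the SAP does not give.

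**What to change.** 1. State in the methods that the primary result is the proportion of the study population with any PD by multidisciplinary discussion, with a two-sided 95% confidence interval.
2. Add an any-PD row at the head of Table 3 and label it the primary result.
3. Add a 95% interval column to Table 3 for overall PD and for every group and subgroup: Wilson in general, Clopper-Pearson for rare subtypes.
4. Optionally, if age, sex and hospital counts of eligible non-participants can be obtained, compare participants with non-participants as a sensitivity analysis and qualify the population-based description accordingly.

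Items 1 to 3 need no new data and cost a sentence, a row and a column. The deviations section shows that results are already known and that Table 3 has become Table 2 in the report. The row and intervals should therefore go into the renumbered table and be listed as an addition. Item 4 depends on eligibility being known for non-participants, which the SAP does not show, so its cost cannot be judged from this document.

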## **Logistical regression: Searching for risk factors that are associated with presence of different forms of PD**

Mock-up Table 4. We aim to explore whether one or more clinical measures collected at baseline are associated with the presence of PD. The dependent variable will be the presence or absence of a PD condition of interest (i.e.,  $Y=1$  if yes, otherwise  $Y=0$ ). Logistic regression is the best approach for identifying predictors when the outcome variable is binary (i.e., presence vs. absence of PD) and the goal is to estimate the association between predictor variables and the probability of the outcome while enabling adjustments for potential confounders. Independent variables, as listed in Table 4 and appendix 3, will be analysed in univariate logistic regression to identify potential associations with clinically significant PD conditions. Odds ratios (ORs) with 95% CIs will be used to quantify the strength of associations, with 95% CIs excluding 1 considered indicative of potential significance. In multiple logistic regression analyses we plan to investigate associations that were significant by univariate analyses, however, only a subset of independent variables will be expected to remain statistically significant and independently associated with PD conditions.

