**Table 2.** Systemic Lupus Erythematosus activity and damage scores, patient reported outcome measures, pulmonary function tests, for all patients and stratified according to presence and absence of pulmonary disease.

| SLE scores, PROMs, and PFT outcomes      | All | PD Present | PD Absent | Contrast between groups (95%CI) |
|------------------------------------------|-----|------------|-----------|---------------------------------|
| SLE disease specific score:       |     |            |           |                                 |
| SLEDAI 2K, score 0-105                   |     |            |           |                                 |
| SLEDAI 2K, without PD, score 0-103       |     |            |           |                                 |
| PGA, score 0-3                           |     |            |           |                                 |
| LLDAS achieved no. (%)                   |     |            |           |                                 |
| DORIS remission achieved no. (%)         |     |            |           |                                 |
| SLICC DI, score 0-48                     |     |            |           |                                 |
| SLICC DI, without PD, score 0-43         |     |            |           |                                 |
| PROMs:                            |     |            |           |                                 |
| LIT, score 0-100                         |     |            |           |                                 |
| SLAQ, score 0-100                        |     |            |           |                                 |
| MRC, score 1-5                           |     |            |           |                                 |
| Dry cough, composite                     |     |            |           |                                 |
| Dry cough, status                        |     |            |           |                                 |
| Never, no. (%)                           |     |            |           |                                 |
| Prior, no. (%)                           |     |            |           |                                 |
| Present, no. (%)                         |     |            |           |                                 |
| Tightness in chest, composite            |     |            |           |                                 |

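### Covariates for the multiple logistic models are chosen on univariate significance alone, so respiratory symptoms and impact scores that PD may cause can be adjusted for in a risk-factor analysis

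*SAP*

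**What the plan says.** The section on logistic regression is subtitled "Searching for risk factors that are associated with presence of different forms of PD". Its outcome is PD or a PD subtype: "The dependent variable will be the presence or absence of a PD condition of interest". It justifies logistic regression as a way to "estimate the association between predictor variables and the probability of the outcome while enabling adjustments for potential confounders".

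The procedure has two steps. First, "Independent variables, as listed in Table 4 and appendix 3, will be analysed in univariate logistic regression to identify potential associations with clinically significant PD", with a 95% CI excluding 1 as the marker of potential significance. Second, "In multiple logistic regression analyses we plan to investigate associations that were significant by univariate analyses". No adjustment set is named, and no class of variable is barred from the second step.

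Table 4 lists dry cough and tightness in chest beside age, sex, disease duration, smoking and overlap disease. Appendix 3 adds MRC, LIT and SLAQ.

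The same five items appear in Table 2. The section behind that table is titled "Analysis methods comparing PD exposed with PD-unexposed" and compares "patient-reported outcome measures, and pulmonary function tests, for all patients and by the presence or absence of thoracic disease".

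**The concern.** Dyspnoea, cough, chest tightness and impact scores are plausibly effects of lung disease. The SAP does not call them that. It is an inference from the nature of the variables and from the SAP's own treatment of PD as the exposure in the Table 2 comparison.

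A variable caused by PD cannot confound the association between a risk factor and PD. If the risk factor also acts on the symptom directly, as smoking may act on cough, the symptom is a common effect of the two. Conditioning on it then changes the association between them. The entry rule looks only at significance, and a variable caused by the outcome is a natural candidate to pass such a screen.

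At stake are the adjusted ORs for the fourth secondary objective. Smoking or overlap disease could be reported as weaker than they are, with a symptom shown as independently associated instead. The primary prevalence estimate is not touched.

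**Working it through.** **Where the variables sit**

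| Variable | Table 2 (by PD status) | Independent variable for PD | Kept out of multiple models? |
|---|---|---|---|
| Dry cough | yes | Table 4 | no |
| Tightness in chest | yes | Table 4 | no |
| MRC, LIT, SLAQ | yes | Appendix 3 | no |
| SLEDAI 2K, SLICC DI | yes | Table 4 and Appendix 3 | no, but versions without PD items are also listed in Table 4 |
| Pleuritis, pleural effusion | no | Table 4 | struck out (/) in the PD and Pleural columns |

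The last two rows show that overlap with the outcome was considered. Nothing similar is done for symptoms or patient-reported measures, and the deviations section does not address it.

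**Inputs.** The SAP states no sample size, PD prevalence or OR, so there is no figure of its own to reproduce. All inputs are assumed: 50% exposed to the risk factor X (say, smoking); logit P(PD) = −0.85 + ln(2.5)·X, which gives PD in about 41%; logit P(symptom) = −1.5 + ln(a)·PD + ln(c)·X, with PD–symptom OR a = 2 or 4 and direct OR c = 1, 1.5, 2 or 3.

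**Formula, one symptom M.** Writing P(m | PD, X):

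OR(X,PD | M=m) = OR(X,PD) × [P(m|1,1)·P(m|0,0)] / [P(m|0,1)·P(m|1,0)]

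**Worked case, a = 4, c = 2.** P(M=1) is 0.1824 with neither PD nor X, 0.3086 with X only, 0.4716 with PD only and 0.6409 with both. The factor is 0.6409 × 0.1824 / (0.3086 × 0.4716) = 0.803, so the adjusted OR is 2.5 × 0.803 = 2.01. The stratum M = 0 gives the same value.

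**Three symptoms.** If they are independent given PD and X, the factor is cubed: 2.5 × 0.803³ = 1.30. Cough, tightness and dyspnoea are unlikely to be independent. The model was therefore refitted on expected cell weights with a shared normal symptom factor, holding the marginal symptom probabilities fixed. The last column takes a correlation of 0.42 to 0.49 between symptoms in patients with neither PD nor X.

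| a | c | One symptom | Three, independent | Three, correlated |
|---|---|---|---|---|
| 2 or 4 | 1 | 2.50 | 2.50 | 2.50 |
| 2 | 1.5 | 2.36 | 2.11 | 2.29–2.30 |
| 2 | 2 | 2.26 | 1.84 | 2.13–2.16 |
| 2 | 3 | 2.11 | 1.50 | 1.92–1.95 |
| 4 | 1.5 | 2.21 | 1.72 | 2.06–2.08 |
| 4 | 2 | 2.01 | 1.30 | 1.78–1.82 |
| 4 | 3 | 1.76 | 0.87 | 1.44–1.49 |

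Weaker correlation lowers the OR further. At 0.24 the last row gives 1.26; full independence is the limit.

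**Subtype models.** The direct route can run through another PD subtype. In a simulation with ILD as outcome and a true OR of 2.0, X also raised airway disease (OR 3 or 5), and both diseases caused cough (OR 6 for airway disease, 4 for ILD). Adjusting for cough moved the OR to 1.82 or 1.72.

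**No direct route.** The OR does not move, but precision can suffer. With three continuous patient-reported scores, each shifted 0.6 SD by PD, the standard error of the log OR rose by 13%.

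**The case against.** The best defence is that the SAP also speaks of predictors and associations, and that its fourth secondary objective explicitly covers outcome measures as well as baseline characteristics. The Introduction wants to help physicians know which PD to suspect. For that diagnostic purpose symptoms are legitimate predictors, and an OR conditional on them is a different quantity, not a biased one. This stands as far as it goes. But the section is subtitled as a search for risk factors and invokes confounder adjustment, so it does not present its model as diagnostic. The objective on outcome measures can be met without using symptoms as covariates for smoking or age.

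It is also fair that entry is not certain. The Introduction notes a substantial gap between patient-reported symptoms and physicians' rating of PD, so symptoms may fail the screen. The SAP also does not say that all significant variables go into one joint model.

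Four stronger readings are tempting but not supported:
- That the univariate ORs are distorted. Table 4 and Appendix 3 adjust for nothing, so this mechanism does not affect them.
- That Table 2 and Table 4 contradict each other. Showing one association as a group contrast and as an OR is not a contradiction.
- That a real risk factor will vanish or reverse. Among the scenarios tabulated, a reversal (0.87) appears only with three independent symptoms and the strongest effects; with symptoms correlated at 0.42 to 0.49 that value is about 1.4 to 1.5.
- That PGA, LLDAS and DORIS are likewise consequences of PD. They measure lupus activity, and their place in the model needs an argument either way.

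**Conclusion.** The concern holds in a conditional form. The entry rule allows respiratory symptoms and impact scores into models meant to find risk factors, and none of the SAP's partial safeguards prevents it. Bias arises if a symptom passes the screen and is fitted together with the risk factor, and if that factor affects the symptom other than through the modelled PD outcome. This is plausible for smoking and cough, and in the subtype models.

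Under the assumed inputs a true OR of 2.5 becomes about 2.4 to 1.8 with one symptom and about 2.3 to 1.5 with three correlated symptoms. It is lower if the symptoms are less correlated, and unchanged at 2.5 without a direct effect. These figures illustrate the mechanism; the SAP has no data to narrow them. The matter should be corrected, but it concerns an exploratory secondary objective.

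**What to change.** In the logistic regression section, replace selection by univariate significance with a pre-specified list for the multiple risk-factor models, limited to variables that can precede PD: for example age, sex, disease duration, smoking, BMI, ethnicity, overlap connective tissue disease, antibodies and complement. State that dry cough, chest tightness, MRC, LIT and SLAQ are not covariates in these models.

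Report those variables as Table 2 contrasts and as univariate ORs, which still serves the objective on outcome measures. If mutually adjusted symptom ORs are wanted, give them in a separate model labelled diagnostic. Justify explicitly any use of lupus activity and damage scores. Where SLEDAI 2K or SLICC DI is used, take the version without PD items.

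The cost is wording and fewer covariates, with no new data. The loss is that the risk-factor model carries no mutually adjusted symptom OR. Because the document already contains a deviations section that reports results, the change should be recorded there, with the list justified by time order and not by the estimates.
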